### Participating surgeons

Studies have found that surgeon proficiency is significantly related to rates of postoperative complications, mortality, and the presence of a residual tumor. Concurrently, a study analyzed surgeons’ operation and found that a surgeon had completed the surgery learning curve after performing 90–100 operations and could independently handle emergencies during surgery [17, 18]. The length of surgery, blood loss, and incidence of intraoperative and postoperative complications similarly decreased. Therefore, all surgeons involved in this study will have completed at least 100 gastrectomy surgeries to ensure the quality of treatment for the enrolled patients. Similarly, our research team includes several experienced gastrointestinal surgeons who are available to perform surgeries for enrolled patients.

### Informed consent

According to the requirements of the ethics committee, all enrolled patients must sign an informed consent document. Informed consent forms are provided to the patients before their enrollment in the prospective study; the consent forms include information on the purpose and significance of the study, the benefits and possible risks of participating in the study, and the confidentiality of the study. Enrolled patients have the opportunity to ask questions and receive answers. The requirement for informed consent is waived due to the retrospective nature of study.

### Interventions

#### D2 gastrectomy

Under the requirement of the guideline for laparoscopic gastrectomy for gastric cancer (2016 edition) [19], laparoscopic radical gastrectomy is performed in patients. A preoperative abdominal enhanced CT scan is performed to evaluate the lesion site, tumor size, and LNM. Preoperative endoscopic injection positioning is performed with dye, or intraoperative endoscopic positioning is used to determine the tumor location to ensure safe margins. The scope of lymph node dissection (LND) is according to the Japanese gastric cancer treatment guidelines 2018 (5th edition) [4]. The scope of LND of D2 distal gastrectomy should include the No. 1, 3, 4sb, 4d, 5, 6, 7, 8a, 9, 11p, and 12a lymph nodes. D2 proximal gastrectomy should include the 1, 2, 3a, 4sa, 4sb, 7, 8a, 9, 11p, and 12a lymph nodes, and D2 total gastrectomy should include the 1, 2, 3, 4sa, 4sb, 4d, 5, 6, 7, 8a, 9, 11p, 11d, and 12a lymph nodes.

#### Perioperative treatment for enrolled patients

For patients who underwent radical surgery, clinicians will provide symptom-based treatment, such as antibiotics, proton pump inhibitors, analgesics, octreotide, total parenteral nutrition support, and blood products, according to the patient’s recovery. Routine postoperative blood tests, biochemistry tests, blood amylase, and abdominal drainage fluid amylase will be reviewed regularly to monitor for anastomotic leakage, delayed bleeding, and pancreatic leakage. There will be a regular abdominal ultrasound examination to monitor for peritoneal effusion. If necessary, drainage by abdominal puncture will be performed. After return to a normal diet, patients with LNM or undifferentiated tumors will receive adjuvant chemotherapy 3–4 weeks after surgery.

#### Data collection

A uniform case report form (CRF) was designed, and the electronic data capture (EDC) system was already established before the commencement of the clinical trial. All data are provided on the CRF. Subsequently, the clinical research coordinator (CRC) enters the data into the EDC system promptly (https://edc-cloud.medsci.cn/#/login). Every month, clinical research associates monitor the electronic database to ensure data quality.

The CRF includes the following data: 1) Demographic information: sex, age, length of hospital stay, body mass index, family disease history, concomitant disease, ECOG score, nutrition risk screening 2002 (NRS 2002) score, and venous thromboembolism score; 2) Perioperative laboratory tests: results of routine blood tests, biochemical investigations, and tumor marker evaluations, including CA19–9, CA125, AFP, CEA, and CA724; 3) Auxiliary examination: all the enrolled patients undergo an abdominal enhanced CT scan and low-dose plain CT scan of the chest, a positron emission tomography (PET)/CT examination when necessary, and an ultrasound gastroscopy or magnified gastroscopy; 4) Surgical information: ASA score, operation date, operation time, blood loss, surgical methods, degree of lymph node dissection, and intraoperative complications; 5) Postoperative pathology: the number of tumor lesions, tumor size, tumor location, surgical margin, gross type of tumor, histopathological type, Lauren type, depth of tumor invasion, number of lymph nodes dissected, and total number of LNM; and 6) Postoperative recovery outcomes: total hospitalization cost, postoperative complications and death, and recovery time of intestinal function (Table 3).

**Table 3 Tab3:** Checklist for the collection of necessary clinical data and follow-up scheme of enrolled patients with EGC

	Baseline information		Follow-up after operation													
	Preoperation	Operation	POD 1	POD 3	POD 7	POD 30	6 months	1 year	18 months	2 years	30 months	3 years	42 months	4 years	54 months	5 years
**Informed consent**	×															
**Demographic information**	×															
**Laboratory tests**	×		×	×	×	×	×	×	×	×	×	×	×	×	×	×
**Chest CT scan**	×							×		×		×		×		×
**Abdominal CT scan**	×						×	×	×	×	×	×	×	×	×	×
**Gastroscopy**	×							×		×		×		×		×
**Abdominal ultrasound**	×						×	×	×	×	×	×	×	×	×	×
**Physical examination**	×						×	×	×	×	×	×	×	×	×	×
**Surgical information**		×														
**Pathology**		×														
**Postoperative recovery outcomes**			×	×	×	×										

× indicates the need to collect the clinical data

POD, postoperative day; EGC, early gastric cancer; Chest CT scan, chest computed tomography scan; Abdominal CT scan, abdominal computed tomography scan

#### Follow-up

The postoperative follow-up is performed by a dedicated investigator. The patients are followed up every 6 months after discharge using outpatient visits, telephone, or mail. During the follow-up period, the patients undergo physical examinations, laboratory tests, a gastroscopy, a chest and abdominal CT scan, or an abdominal ultrasound assessment. The laboratory tests include routine blood examination, blood biochemistry, and tumor marker evaluation that includes CA19–9, CA125, AFP, CEA, and CA724. For patients that develop postoperative tumor recurrence or distant metastasis, a further detailed evaluation, including abdominal magnetic resonance imaging or PET/CT, will be performed to determine the feasibility of surgical resection. Each patient will be followed for at least 5 years or until a loss to follow-up. The detailed follow-up schedule is shown in Table 3.

#### Adverse events

All serious adverse events (SAEs) occurring between the signing of the informed consent and the completion of the trial need to be recorded. SAEs are defined as any injury related (or not) to the expected outcome of the operation. The trial includes an independent data monitoring committee that will review the ongoing safety data in an unblinded manner under the Standard Operation Procedures for Clinical Trials, Japan Medical Association. All the patients will undergo the best treatments for curing complications.

### Quality control

#### Quality control of pathology

The specimen collectors have sampling experience or are guided by an experienced pathologist. The procedures for handling the resected specimens are as follows: First, the pathologist incises the stomach along the greater curvature. Second, the specimen is fully stretched to maintain the original shape, and the stomach is placed on a flat rubber plate with the mucosal side up and pinned at the edge with stainless steel pins. At the edge of the specimen, the entire gastric wall, especially the muscularis, is pulled outward by the needle with a uniform force to extend the mucosa, which is subsequently fixed on the rubber plate to fully expose the lesions of the mucosal surface. Third, the specimen collection is performed within 30 min after the tissue is isolated. Thereafter, we completely immerse the specimen in a volume of 10% neutral buffered formalin 6–8 times that of the specimen for 12–48 h. The tumor lesions are afterwards sectioned along the vertical direction of the tangent line near the cutting edge. Subsequently, the whole gastric wall tissue is cut in parallel at a distance of 4–5 mm, and all tissues are collected for examination. Finally, we dehydrate, embed, and section the tissue for microscopic observation. The detailed procedure is illustrated in Fig. 2.

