### Inclusion criteria

Patients aged 18–75 years (regardless of sex).Patients with Eastern Cooperative Oncology Group (ECOG) score ≤ 2 points and American Society of Anesthesiologists (ASA) score ≤ 2 points who can undergo a radical D2 gastrectomy.Patients without a history of gastrointestinal operation, chemotherapy, or radiotherapy.Patients with normal liver, kidney, heart, lung, and bone marrow function (GPT × 10^9^/L, PLT>10^9^/L).Patients who can understand and comply with the research protocol.Patients who can provide written informed consent by themselves or through their legal agent.Gastroscopic and pathologic diagnoses based on the following criteria: ①Tumor diameter > 30 mm, ulceration (UL)(+), and differentiated, mucosal carcinoma (T1a); ②Tumor diameter > 30 mm and differentiated, submucosal invasion depth < 500 μm (T1b SM1); ③Tumor diameter ≤ 30 mm and differentiated, submucosal carcinoma (T1b); ④Tumor diameter ≤ 20 mm, UL(−), and undifferentiated (T1a); ⑤Tumor diameter > 20 mm, UL(−), and undifferentiated (T1a); ⑥Tumor diameter ≤ 30 mm, UL(+), and undifferentiated (T1a); ⑦Tumor diameter > 30 mm, UL(+), and undifferentiated (T1a). The detailed inclusion criteria are shown in Table 1.

**Table 1 Tab1:** Inclusion criteria of expanded indications for ESD in patients with EGC

	T1a				T1b			
	UL (−)		UL (+)		SM1		SM2	
	≤20 mm	> 20 mm	≤30 mm	> 30 mm	≤30 mm	> 30 mm	≤30 mm	> 30 mm
**Differentiated**	ESD	ESD	ESD	EXPANDED	EXPANDED	EXPANDED	EXPANDED	SURGERY
**Undifferentiated**	EXPANDED	EXPANDED	EXPANDED	EXPANDED	SURGERY	SURGERY	SURGERY	SURGERY

ESD, ESD absolute indication; EXPANDED, ESD expanded indication; SURGERY, surgical indication for EGC; EGC, early gastric cancer; ESD, endoscopic submucosal dissection

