**Fig. 2 Fig2:**
[figure not shown]
Standardized procedure for sampling of gastric specimen by surgical resection: **a** incision of the specimen along the greater curvature of the stomach; **b** the resected specimen was pinned out with fine needles on a rubber plate; **c** the resected specimen was soaked in a volume of 4% neutral buffered formaldehyde 6–8 times that of the specimen for 12–48 h; **d** and **e** the whole of the gastric wall tissue was sliced in parallel at a distance of 4–5 mm; **f** the sliced tissues were placed in the cassettes for subsequent dehydration, embedding, and sectioning for histological evaluation

Moreover, we have developed a standardized pathology report template to homogenize the data from all research centers. The pathology report includes the macroscopic description, histological diagnosis, Lauren type, depth of invasion, vascular-lymphatic infiltration, surgical margin, LNM, pathological tumor stage, immunohistochemical staining, and gene detection.

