## Discussion

The optimal treatment for EGC should balance radical tumor treatment and surgical trauma reduction. However, controversy remains surrounding how to choose an appropriate treatment in patients with EGC who exceed the absolute indications for ESD. The primary endpoint of this study is the rate of LNM. The scope of potential expanded indications for ESD will be explored and evaluated based on the presence of LNM by histopathology and the positive rate of LNM with expanded indications for ESD. The purpose of this study is to explore and evaluate expanded indications for ESD that match the characteristics of the Chinese population in patients with EGC and to introduce a staging diagnosis and examination scheme for EGC that is appropriate for China. To the best of our knowledge, this study is the first clinical trial to focus on Chinese patients with EGC, and the results could facilitate clinical decision-making.

Despite decades of research on the treatment of EGC, numerous problems remain unsolved. Regarding preoperative evaluation, Choi et al. showed that the overall accuracy of endoscopic ultrasonography in T staging of gastric cancer is 78% and only 72% in T1b submucosal staging. Thus, determining the depth of tumor submucosal infiltration remains difficult, which may result in unnecessary surgical trauma to some patients [22]. Similarly, Choi et al. reported that the tumor diameter measured under the endoscope was significantly smaller than that measured pathologically. Although the size deviation in 80% of tumor lesions was < 0.4 cm, the difference suggests that preoperative gastroscopy may underestimate the tumor diameter [23]. Consequently, ESD performed in patients with expanded indications may result in non-curative resection of the tumor and, thereby, affect the prognosis of patients.

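### The written specimen procedure opens every stomach along the greater curvature, so a lesion on that line is divided before its pathological size and depth are determined

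*Protocol article*

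**What the plan says.** Under Quality control of pathology, the protocol article sets out the handling of resected specimens as an ordered sequence. The opening step is "First, the pathologist incises the stomach along the greater curvature". The legend of Fig. 2, which presents the standardized sampling procedure, gives the same step as panel a: "incision of the specimen along the greater curvature of the stomach". Neither place attaches a condition about where the tumour lies.

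The opened stomach is then stretched, laid mucosa upwards on a rubber plate and pinned round its edge, with the full wall drawn outward at that edge. Formalin fixation for 12–48 h follows. Only then does the lesion itself come up: "The tumor lesions are afterwards sectioned along the vertical direction of the tangent line near the cutting edge". The wall is cut into parallel slices 4–5 mm apart, all tissue is taken, and microscopy comes last: "Finally, we dehydrate, embed, and section the tissue for microscopic observation".

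The Data collection section lists among the postoperative pathology items "the number of tumor lesions, tumor size, tumor location, surgical margin, gross type of tumor", and also depth of invasion. Inclusion criteria and Table 1 place patients in categories by size (limits at 20 and 30 mm), depth (T1a, SM1, SM2), ulceration and differentiation. The basis is described as "Gastroscopic and pathologic diagnoses based on the following criteria". Secondary endpoints names postoperative histopathology as the standard against which ultrasound gastroscopy is judged for depth.

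**The concern.** A single opening line for all specimens suits most tumour sites but not one predictable group. If the lesion lies on the greater curvature, the first cut passes through it. The cut edges of the tumour then become part of the edge of the opened specimen, and that edge is the part drawn outward and pinned. The two parts of the lesion end up on opposite sides of the plate, the maximum diameter has to be pieced together, and an unplanned cut, made before fixation, runs through tissue on which depth may need to be read. The purpose of the pinning step, to display the lesion fully, is not met for these tumours.

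At stake are two of the variables that define the Table 1 cells. A distorted size or depth could put a patient in the wrong cell, and so affect the LNM rate reported for that cell and any LNM cut-off drawn on size or depth. A distorted depth reading would also be counted as an error of ultrasound gastroscopy, because pathology is the reference. Any such error would be tied to tumour site, not spread at random over the cohort.

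**Working it through.** The plan gives no figure to reproduce on this point. The check is a reading of the order of steps, followed by one range under a stated assumption.

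1. **Can such tumours be enrolled?** The Inclusion, Exclusion and Elimination criteria do not restrict site within the stomach. Greater-curvature lesions are therefore eligible.

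2. **Does the cut precede measurement on the specimen?** The written order is: open, stretch and pin, fix, slice, microscopy. Depth is necessarily read at the end. The article does not say when specimen size is taken, but its first step is the incision and no measurement is placed before it.

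3. **Do size and depth move a patient between Table 1 labels?**
   - Size at 30 mm: differentiated T1a with ulceration changes from ESD (≤30 mm) to EXPANDED (>30 mm). Differentiated SM2 changes from EXPANDED (≤30 mm) to SURGERY (>30 mm).
   - Size without a change of label: undifferentiated T1a stays EXPANDED, but crossing 20 mm (no ulceration) or 30 mm (ulceration) moves the patient between separately listed inclusion categories.
   - Depth: undifferentiated T1a against T1b is EXPANDED against SURGERY. Differentiated tumours >30 mm at SM1 against SM2 are EXPANDED against SURGERY.
   - Some boundaries change nothing. Differentiated T1a without ulceration is ESD on both sides of 20 mm, and differentiated T1b ≤30 mm is EXPANDED at SM1 and SM2 alike.

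4. **What is not affected?** Nodal status is read on the lymph nodes, so the overall LNM rate does not depend on how the stomach is opened. Differentiation is not obviously affected either.

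5. **How many specimens could a change of rule reach?** Determination of sample size splits the 554 patients into 274 prospective and 280 retrospective (274 + 280 = 554). Study design and setting dates the retrospective patients January 2008 to April 2018, and protocol version 1.0 is from April 2018. Nothing shows that this procedure governed the earlier specimens, and they cannot be reopened differently. The relevant base is therefore at most 274. The documents give no share of tumours on the greater curvature. As an assumption, take 5–20%:
   - 0.05 × 274 = 13.7, about 14
   - 0.20 × 274 = 54.8, about 55

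6. **How large is the error per specimen?** The documents contain no figure for the error made when a divided lesion is pieced together. It cannot be estimated here.

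**The case against.** The strongest reply is that this is bench detail which a journal article leaves to a fuller document. Research supervision committee says that each part of the trial has a standard operating procedure, and Quality control of pathology says that those taking the specimens are experienced or guided by an experienced pathologist. A site exception may exist, and experienced staff may apply one unprompted. That may reduce the harm. It does not change the written rule: the article sets the procedure out down to formalin volume and slice spacing, presents it as the standard, and fixes the opening line without a condition. If an exception exists elsewhere, one clause brings the two into line.

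The reply also limits the size of the point, and these limits stand:

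- The category does not rest on the opened specimen alone. The criteria combine gastroscopic and pathological diagnosis, and Quality control of gastroscopy records site and size before surgery (and depth where ultrasound gastroscopy is done).
- Every lesion is later sliced through its full thickness at 4–5 mm, with all tissue taken. One further cut leaves depth largely readable.

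Three stronger readings are tempting, and the documents do not support them:

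- A reader might apply the assumed share to the whole sample. The rule cannot be changed for the retrospective specimens, and it is not shown to have governed them.
- A reader might take the remark in the Discussion that "the size deviation in 80% of tumor lesions was < 0.4 cm" as a yardstick for the error from a divided lesion. It describes endoscopic against pathological size in a cited study and says nothing about piecing a lesion together.
- A reader might say that an endpoint on the accuracy of size is compromised. Secondary endpoints lists depth, LNM, differentiation and TNM staging. Size is not among them.

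**Conclusion.** The point holds as a flaw in a stated rule with limited reach. As written, the standardized procedure divides a lesion on the greater curvature before its pathological size is measured and its depth sectioned. The result is a risk, not a certainty, of distorted size near 20 or 30 mm and, to a lesser extent, of a distorted depth reading. What it can touch is the Table 1 category, the category-specific LNM rates, the LNM cut-offs, and the depth reference for ultrasound gastroscopy. The overall LNM rate, which is the primary endpoint, is untouched.

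The figure of about 14–55 of 274 prospective patients rests wholly on the assumed 5–20% share, and it counts divided lesions, not misclassified patients. How many of these would change cell is unknown. The change is worth making because the affected group is predictable, its site is already recorded, and the remedy costs almost nothing.

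**What to change.** Amend the first step under Quality control of pathology, and panel a of Fig. 2, to read along these lines: *open along the greater curvature unless the lesion lies on or next to it, in which case open along a line that does not cross the lesion; record the maximum diameter on the undivided lesion.*

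For specimens already opened through the lesion, including retrospective ones where this is recorded, add a flag and repeat the depth-accuracy and category-specific LNM analyses without them. The study began in May 2018 and the article appeared in August 2020, so some of the 274 prospective specimens may already be in this position; the documents do not say how many.

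The cost is one clause, one field on the pathology form and one small sensitivity analysis. Tumour site is already recorded at gastroscopy and at pathology, so no further data are needed to apply the exception.

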**Fig. 2 Fig2:**
[figure not shown]
Standardized procedure for sampling of gastric specimen by surgical resection: **a** incision of the specimen along the greater curvature of the stomach; **b** the resected specimen was pinned out with fine needles on a rubber plate; **c** the resected specimen was soaked in a volume of 4% neutral buffered formaldehyde 6–8 times that of the specimen for 12–48 h; **d** and **e** the whole of the gastric wall tissue was sliced in parallel at a distance of 4–5 mm; **f** the sliced tissues were placed in the cassettes for subsequent dehydration, embedding, and sectioning for histological evaluation

Moreover, we have developed a standardized pathology report template to homogenize the data from all research centers. The pathology report includes the macroscopic description, histological diagnosis, Lauren type, depth of invasion, vascular-lymphatic infiltration, surgical margin, LNM, pathological tumor stage, immunohistochemical staining, and gene detection.

#### Quality control of gastroscopy

We have developed a gastroscopy report template, which helps to unify the research data; the report includes a general description of the stomach. We need to obtain 4–8 images of the different parts of the stomach. Furthermore, the report describes the number of lesions, tumor location, tumor size, gross type of tumor, tumor distance from the dentate line, and tumor distance from the pyloric ring. If patients undergo ultrasound gastroscopy, the report should equally describe the depth of invasion and the occurrence of LNM around the stomach.

